**Box 1: Some unique characteristics of studies conducted using NCSS protocols**

Geographically diverse populations

Large, population-based, sample size with severe morbidity and mortality outcomes

Early pregnancy dating by ultrasound provided by small number of standardised operators

Standardised methodology for maternal, newborn and infant follow-up anthropometric measures

Maternal morbidities during pregnancy captured prospectively

Environmental characterisation of the populations and individual participants

However, we recognise the need to enrich the collection of complicated pregnancies from populations with other risk factors that are especially relevant to the needs of developing countries. Therefore, we will supplement sample collection in the three INTERGROWTH-21st centres by also collecting samples from pregnancies from the general population in resource-poor settings where there is a high risk of fetal growth impairment and preterm delivery because of infection, malnutrition, poor socio-economic status and past adverse pregnancy outcomes. This strategy will increase the generation of cases from a relatively small population given the higher incidence of the conditions.

In these centres, we will collect and store samples from 800 pregnancies per centre:

Maternal blood, maternal faeces, cord blood and placental samples will be collected from pregnancies (cases) that have delivered at  $<38^{+0}$  weeks gestation ( $n=200$  per centre) or have resulted in IUGR/SGA newborns ( $n=200$  per centre). Newborns that were born at  $<38^{+0}$  weeks' gestation and were IUGR/SGA will be included in both sets of cases as the case-control analysis will be carried out separately for each outcome.

We will also collect the same samples from term AGA newborns (controls), i.e. non-IUGR, normal birth weight newborns at term, as a reference group ( $n=400$  per centre, i.e. one control for each case).

All cases and controls are required to have had, reported in their medical records, an estimation of gestational age by ultrasound measurement of either CRL  $<14$  weeks or HC  $<24$  weeks. When LMP is available this should also be recorded. If the LMP is not available it should be recorded as such and ultrasound estimations will be used.

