#### **On-line data management and statistical analysis**

All clinical data will be entered into an on-line data management system specifically developed for the study. It includes a method for direct transfer of blinded data from the ultrasound machines to the database. This on-line system has the practical benefit of allowing on-going quality control, correction of errors or missing values and the initiation of data analysis soon after data collection is completed. It will be used for data management and monitoring all sub-studies, including patient recruitment and follow-up, and is based on the INTERGROWTH-21st Electronic Data Management System. The system permits all participants' data to be incorporated into the data files via the Internet as soon as they are available. Included within the system is a review process to ensure that all data are complete.

All sample related data will be entered separately into a data management system specifically developed for the study. The system allows samples to be tracked from the time of collection through processing, storage in the participating centres, and transport to a centralised facility. Each participant will have a unique identifier number, which will be used to link the clinical and sample databases. The number will also be used to barcode individual samples and aliquots. Quality control for this aspect of the study will be monitored by a team from GAPPS.

These systems will provide the Data Management Unit with a detailed daily record of patient enrolment and data entry, at both individual and institutional levels to monitor progress against the milestones listed in the protocol. Corresponding actions, such as telephone calls, web conferences and site visits will take place within a week of detecting a problem in a centre to ensure that appropriate corrective measures are taken.

d Others have also used these composite indices of neonatal morbidity (Hannah ME, Hannah WJ Kewson SA et al (2000); Wapner RJ, Sorokin Y, Thom EA (2006); Joseph KS, Fahey J, Platt R (2009)).

**Selection of Cases and Controls** All live and stillborn infants in the study hospitals during the data collection period, whether or not they survive until hospital discharge, will be screened. However, multiple births and post-term births ( $>42^{+0}$  weeks), will not be included.

Each newborn infant will fall into one of the four groups below:

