#### Operational definition of cases and controls in the maternity wards

To simplify the identification of cases and controls during screening, the following procedures will be used (see instructions in Appendix II):

First, gestational age will be assessed using CRL or HC. **Cases, born at  $<38^{+0}$  weeks, will be live or stillborn infants with gestational age assessed by an early ultrasound (either CRL at  $<14$  weeks or HC at  $<24$  weeks)**, regardless of whether or not they presented with IUGR/SGA at any time during pregnancy or at birth. These infants correspond to groups A and C in the table above.

Second, BW for gestational age will be assessed for infants born  $\geq 38^{+0}$  weeks. **Cases, IUGR/SGA, will be live or stillbirths whose BW for gestational age is below the 10th centile of the INTERGROWTH-21st neonatal standard as defined on the form.** These infants correspond to group B in the table above. In the data analysis phase, infants from group C (IUGR/SGA infants born  $<38^{+0}$  weeks) will be added to those in group B so as to include all IUGR/SGA infants regardless of their gestational age at birth.

Third, the screening form will also identify **potential controls, that is, non-IUGR/SGA infants who were not born  $<38^{+0}$  weeks** (group D in the table above). The first potential control born after each case (either a case born  $<38^{+0}$  weeks or an IUGR/SGA case) in the same hospitale will be enrolled in the study as a control. After enrolling a case, a control must be recruited. If two cases are born in succession, the second case cannot be recruited and instead screening for a control continues. Once a case-control pair have been recruited and processed, sites then screen for another case.

At each site, 200 cases born  $<38^{+0}$  weeks and 200 IUGR/SGA cases will be recruited, along with 400 controls. If a site collects 200 cases born  $<38^{+0}$  weeks before it has collected 200 IUGR/SGA cases, it will stop recruiting cases born  $<38^{+0}$  weeks and their corresponding controls, and will continue recruiting IUGR/SGA cases until 200 (and their controls) have been recruited - and vice-versa, if the quota of 200 IUGR/SGA cases is collected before 200 cases born  $<38^{+0}$  weeks are enrolled.

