### Definitions of cases and controls for the data analyses

Cases born  $<38^{+0}$  weeks' gestation for the data analyses will include all births at  $<38^{+0}$  weeks whether or not they present with IUGR/SGA (groups A and C).

IUGR/SGA cases for the data analyses will include the operational definition of IUGR/SGA cases (group B) plus those cases born  $<38^{+0}$  weeks who are also IUGR/SGA (group C); the latter were collected as a sub-set of cases born  $<38^{+0}$  weeks.

Infants in group C (IUGR/SGA infants born  $<38^{+0}$  weeks) will be included in both groups of cases, as the case-control analyses will be carried out separately for each outcome.

The table below provides the definition of controls for the analyses.

Controls for cases born  $<38^{+0}$  weeks will be a sample of live and stillborn infants born  $\geq 38^{+0}$  weeks. In the statistical analyses, a proportion of term IUGR/SGA (xB) cases will be added to the operational controls (group D).

Controls for IUGR/SGA cases will be a sample of live and stillborn infants who are not IUGR/SGA at birth. In the analyses, they will include all operational controls (group D) plus a proportion of infants born  $<38^{+0}$  weeks who are not IUGR/SGA at birth (xA).

Table 2. Case-control comparisons in the data analyses.

| Comparison                                       | Cases | Controls | Comments                                                                                                                                                                                                                                                     |
|--------------------------------------------------|-------|----------|--------------------------------------------------------------------------------------------------------------------------------------------------------------------------------------------------------------------------------------------------------------|
| Infants born $<38^{+0}$ weeks case-control study | A + C | D + xB   | To reproduce the control population, set B (IUGR/SGA only) will be down-weighted by a factor x which is equal to the sampling fraction for set D, that is the proportion of all infants in the control pool who were included in the detailed study (cases). |

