| IUGR/SGA case-control study                      | B + C | D + xA   | As above, for set A (infants born $<38^{+0}$ weeks only).                                                                                                                                                                                                    |

Subgroup analyses will include cases born  $<38^{+0}$  weeks, stratified according to: a) gestational age groups (the exact groupings will be decided based on the number of births each week of gestational age, so that there will be at least 100 cases in each sub-group) or b) by preterm phenotype, using the newly proposed INTERGROWTH-21st classification system. For IUGR/SGA, subgroup analyses will include stratification by: a) IUGR/SGA severity ( $<3^{rd}$ , 3-5th, 6th-9th centiles) and b) gestational age.

Appendix II provides more detailed information on different strategies for selecting controls for case-control studies than we considered when planning the study, but some of these proposed strategies were not practical. As proposed above, INTERBIO-21st will adopt a traditional case-non-case design, and odds ratios will be used to estimate relative risks. This is based on the assumption that cases will be relatively rare, i.e.  $<10\%$  of the overall number of births.

We estimate that the overall birth rate for infants born  $<38^{+0}$  weeks will be  $<10\%$  and the overall IUGR/SGA rate will be  $<10\text{--}15\%$ . However, by collecting data on all four sets (A, B, C and D), it will also be possible, with appropriate statistical weights in the analyses, to carry out case-base analyses using Poisson regression with robust variance, if the outcomes end up being more common ( $>10\%$ ).

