### Sample processing

The sample collection, processing and storage procedures will be performed in a standardised manner based on protocols described in detail in the INTERBIO-21st Operations Manual that has been developed with the assistance of the GAPPS team, and researchers at the Universities of Oxford and Cambridge, and Johns Hopkins Bloomberg School of Public Health.

In brief, maternal and cord blood samples will be collected to store whole blood, plasma and the buffy coat for a wide range of purposes, including DNA extraction for genetic and epigenetic studies and micronutrient assays. Two placental biopsies will be taken for immunohistochemistry and DNA extraction and in RNA later for expression studies (if the sample is obtained  $<30$  mins after delivery). In addition, we intend to collect and store samples for a number of future, as yet unspecified, biomarker assays relating to preterm delivery and fetal growth.

It is vitally important to ensure that samples are collected in a standardised way with adequate monitoring of quality control, principally because sample quality, quantity and handling can greatly influence the results of microarray and sequencing experiments.

The primary reason (aside from quality control) for ensuring that samples are collected, stored and processed in a uniform manner is to facilitate the anticipated interchange of data, in the future, with other biobanks. Standardising phenotypic definitions, sample collection methods and analyses fosters trans-national collaboration and networking. We shall therefore also seek advice from groups such as the Public Population Project in Genomics (<http://www.p3g.org>), which promotes international harmonisation and collaboration in population genomics and biobanking by sharing research tools and expertise.

**Faecal samples:** We wish to collect a faecal sample from mothers, opportunistically at the time of delivery, for metabiomic studies. Although it has been suggested that we should also collect stool samples from infants every 6 months, we feel that this is a rather large-scale undertaking that is beyond our remit.

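### Appendix K pools stillborn and live-born infants in cord-blood and placental comparisons, so tissue changes after fetal death can pass for markers of early birth or SGA

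*Protocol*

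**What the plan says.** All references are to Appendix K of the Protocol unless stated otherwise.

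- **Screening** (Selection of Cases and Controls) is stated thus: "All live and stillborn infants in the study hospitals during the data collection period, whether or not they survive until hospital discharge, will be screened".
- **Recruitment definitions** (Operational definition of cases and controls in the maternity wards): early-birth cases, before 38+0 weeks, "will be live or stillborn infants with gestational age assessed by an early ultrasound". IUGR/SGA cases "will be live or stillbirths whose BW for gestational age is below the" 10th centile.
- **Analysis definitions** (Definitions of cases and controls for the data analyses): the group born before 38+0 "weeks' gestation for the data analyses will include all births at" that limit (sets A + C). The IUGR/SGA cases are sets B + C. On the other side, "Controls for IUGR/SGA cases will be a sample of live and stillborn infants who are not IUGR/SGA at birth"; controls for early births are likewise live and stillborn.
- **Material** (text following Box 1): "Maternal blood, maternal faeces, cord blood and placental samples will be collected from pregnancies (cases" in either group), and the same samples from controls. Under Sample processing: "Two placental biopsies will be taken for immunohistochemistry and DNA extraction and in RNA later for expression studies". The only time limit, under 30 minutes for the expression sample, runs from delivery.
- **What is separated**: analyses are stratified by centre. Early births may be split by gestational age or preterm phenotype. "For IUGR/SGA, subgroup analyses will include stratification by: a) IUGR/SGA severity" and gestational age. Matching is on hospital and approximate date of birth only.
- **Programme II** draws 500 term IUGR/SGA cases at random from the bank, with 500 normal birth weight controls. It plans neonatal body composition for all of them.

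**The concern.** Vital status bears on the state of the tissue. After antepartum death, cord blood and placenta may stay in the uterus for hours or days before delivery, and a clock that starts at delivery does not see that interval. Sample processing itself warns that sample quality and handling can greatly influence array and sequencing results.

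Bias needs two conditions. Fetal death must be more frequent among cases than controls, and death must alter the assayed marker. The first is likely when cases are defined by early birth or small size. The second will vary from marker to marker. Where both hold, a difference caused by death would be reported as a difference associated with preterm delivery or growth restriction. Centre strata and matching on hospital and date do not remove it, because neither is related to vital status.

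This is not a detail left for later: the section that defines the groups for the data analyses fixes the pooling.

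**Working it through.** **1. The plan's own figure.** Table 1 gives 719 cases for a methylation proportion of 0.2 in controls against 0.3 in cases (alpha 0.0005, 80% power, 1:1). The two-sided two-proportion formula with continuity correction returns 719, so the same alpha, background proportion and normal approximation are used below.

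**2. Inputs.**
- Stillbirth rate *r*: not given for INTERBIO. Assumed 0.5%, 1% or 2%. The main protocol expects perinatal mortality close to 1% and requires below 20 per 1,000, but those figures include neonatal deaths and describe low-risk institutions, so they give an order of magnitude only.
- Share of stillbirths in the early group: assumed 70%. The main protocol's NCSS sample size puts 70% of severe outcomes, a composite that includes stillbirth, at 26-36 completed weeks.
- Births before 38+0: taken as 10%. Appendix K expects under 10%, and a lower rate would raise the stillbirth share among cases.
- Marker 'on' in 0.2 of live births (Table 1) and in a proportion *q* of stillbirths (assumed 0.3 to 1.0). No true case-control effect.

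**3. Stillbirth shares.** Cases: s1 = 0.7r/0.10. Births at or after 38+0: s0 = 0.3r/0.90, so stillborn controls are counted.

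| r | s1 | s0 |
|---|---|---|
| 0.5% | 3.5% | 0.17% |
| 1% | 7% | 0.33% |
| 2% | 14% | 0.67% |

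**4. Spurious difference and false-positive rate, early-birth comparison.** d = (s1 - s0)(q - 0.2). With n per group, the rejection probability is Φ[(d - z·SE0)/SE1] + Φ[(-d - z·SE0)/SE1], where z = 3.48, SE0 uses the pooled proportion and SE1 the separate ones.

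Example, r = 1%, q = 0.8, n = 1,000: p1 = 0.2 + 0.6 × 0.07 = 0.242; p0 = 0.2 + 0.6 × 0.0033 = 0.202; d = 0.040; SE0 = SE1 = 0.0186 to four decimals; (0.040 - 0.0647)/0.0186 = -1.33; probability 0.092.

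| r | q | d | Spurious OR | Rejection rate at 0.0005, 1,000 v 1,000 |
|---|---|---|---|---|
| 0.5% | 0.3 | 0.003 | 1.02 | 0.0006 |
| 0.5% | 0.5 | 0.010 | 1.06 | 0.0017 |
| 0.5% | 0.8 | 0.020 | 1.13 | 0.0085 |
| 1% | 0.5 | 0.020 | 1.13 | 0.0085 |
| 1% | 0.8 | 0.040 | 1.26 | 0.092 |
| 2% | 0.8 | 0.080 | 1.55 | 0.75 |
| 2% | 1.0 | 0.107 | 1.76 | 0.98 |

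If s1 = s0, or if q = 0.2, then d = 0 and the rate stays at 0.0005.

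**5. Programme II (term only).** As a bound, suppose every stillbirth at or after 38+0 is SGA, SGA is 10% of those births, and no control is stillborn. The stillborn share of cases is then s0/0.10 = 1.7%, 3.3% or 6.7%. At q = 0.8, d = 0.6 × share = 0.010, 0.020 or 0.040, and the rejection rate at 500 v 500 is 0.0011, 0.0034 or 0.025. At q = 1.0, d = 0.8 × share = 0.013, 0.027 or 0.053. All lie below the smallest difference in Table 1, which is 0.10.

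**6. Cost of a live-birth analysis.** Removing 3.5-14% of 1,000 early cases leaves 965-860. With equal numbers of controls, power for 0.2 v 0.3 at 0.0005 falls from 95.5% to 94.6-90.6%.

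**The case against.** The strongest reply is about size and mechanism. No stillbirth rate is given for the INTERBIO centres, and nothing says how often stillbirths would be enrolled and sampled. The documents do not say that methylation or micronutrient values change after fetal death. Intrapartum deaths, which Appendix K discusses when defining its composite outcome, involve little delay before delivery. All of this stands, and it is why the result is a range that starts at negligible.

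It can also be said that sampling detail sits in an Operations Manual not shown here, that the content of the preterm-phenotype classification is not shown, and that stillbirth is a recorded outcome, so a live-birth analysis remains possible. That is true and makes the repair easy. It does not alter the analysis definitions, which combine live births and stillbirths.

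Four stronger readings are tempting, and the documents do not support them.

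- *Only cases can be stillborn.* Controls are eligible too. The problem is unequal frequency, not unequal eligibility.
- *Death alone could produce the differences Table 1 is powered for.* Only the extreme corner (2% stillbirth, marker switched on in all) reaches 0.10, and only for births before 38+0. Table 1 is applied first to Programme II, which is term-only.
- *Stillbirths should be dropped from every sample-based comparison.* Post-mortem change in fetal tissue is no reason to drop maternal blood or faeces. Restricting to live births also conditions on survival and may remove the most severely growth-restricted cases.
- *Stillborn infants become SGA through delay alone, so size should be dated at last confirmed life.* Growth stopping before delivery is a fair worry, but Neonatal Study mothers are screened on admission for delivery, and even Fetal Study scans are about five weeks apart. That date could precede death by weeks and misclassify in the other direction.

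**Conclusion.** The point holds in a limited form. The stated definitions pool live-born and stillborn infants for cord-blood and placental assays, and no stated stratum, matching factor or timing rule separates them by vital status. Controls may be stillborn as well, but fetal death is likely to be concentrated in the case groups.

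The direction of the risk is clear; its size is not. For early-birth cases it runs from no practical effect (0.5% stillbirth, marker barely altered) to a false-positive rate of 0.092 at 1% stillbirth with the marker on in 80% of stillbirths, and beyond that in the extreme corner. In Programme II it is smaller: a difference of at most 0.04 at q = 0.8 under the bound used. These figures rest on the assumed stillbirth rates, the 70/30 split and *q*, none of which the documents supply for INTERBIO. The point does not invalidate the design, but it is a foreseeable bias that can be checked cheaply.

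**What to change.** 1. For Table 2 and Programme II comparisons that use cord blood or placenta, record vital status and, for stillbirths, whether death was antepartum or intrapartum, with its timing where known.
2. Prespecify a live-birth-only analysis and report it beside the all-births analysis. Report a cord or placental marker as associated with early birth or SGA only if it persists among live births, with the criterion for persistence written beforehand.
3. In Programme II, state that the 500 cases and 500 controls are live-born, which agrees with the neonatal body composition already planned for them.
4. Keep stillbirths in the clinical risk-factor, maternal blood and maternal faecal analyses, and leave their size classification as it is.

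The cost is a few sentences and one or two data items. The live-birth analysis of early births loses about 3.5-14% of cases under the assumed rates, with the modest loss of power shown above. Programme II should lose nothing: Appendix K foresees 1,000 term IUGR/SGA newborns, and even with 6.7% stillborn about 933 live-born remain from which to draw 500. The real drawback is conditioning on survival, which is why both analyses should be shown.

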#### Operational definition of cases and controls in the maternity wards

To simplify the identification of cases and controls during screening, the following procedures will be used (see instructions in Appendix II):

First, gestational age will be assessed using CRL or HC. **Cases, born at  $<38^{+0}$  weeks, will be live or stillborn infants with gestational age assessed by an early ultrasound (either CRL at  $<14$  weeks or HC at  $<24$  weeks)**, regardless of whether or not they presented with IUGR/SGA at any time during pregnancy or at birth. These infants correspond to groups A and C in the table above.

Second, BW for gestational age will be assessed for infants born  $\geq 38^{+0}$  weeks. **Cases, IUGR/SGA, will be live or stillbirths whose BW for gestational age is below the 10th centile of the INTERGROWTH-21st neonatal standard as defined on the form.** These infants correspond to group B in the table above. In the data analysis phase, infants from group C (IUGR/SGA infants born  $<38^{+0}$  weeks) will be added to those in group B so as to include all IUGR/SGA infants regardless of their gestational age at birth.

Third, the screening form will also identify **potential controls, that is, non-IUGR/SGA infants who were not born  $<38^{+0}$  weeks** (group D in the table above). The first potential control born after each case (either a case born  $<38^{+0}$  weeks or an IUGR/SGA case) in the same hospitale will be enrolled in the study as a control. After enrolling a case, a control must be recruited. If two cases are born in succession, the second case cannot be recruited and instead screening for a control continues. Once a case-control pair have been recruited and processed, sites then screen for another case.

At each site, 200 cases born  $<38^{+0}$  weeks and 200 IUGR/SGA cases will be recruited, along with 400 controls. If a site collects 200 cases born  $<38^{+0}$  weeks before it has collected 200 IUGR/SGA cases, it will stop recruiting cases born  $<38^{+0}$  weeks and their corresponding controls, and will continue recruiting IUGR/SGA cases until 200 (and their controls) have been recruited - and vice-versa, if the quota of 200 IUGR/SGA cases is collected before 200 cases born  $<38^{+0}$  weeks are enrolled.

e If there is more than one hospital at a given study site, and if presumed risk factors vary by hospital (e.g. one primarily attracts mothers of low socioeconomic status, and another attracts high income mothers), it may be necessary to weight the analyses to reproduce a control group that is representative of the study population; ignoring such differences may lead to overmatching.

Note that the only criteria for matching cases and controls are: a) hospital of birth and b) approximate date of birth (usually same day, sometimes the next day if there are no controls on the same day).

